#### Participant Testing in the Community

##### Overview

The research team will conduct a web-based training session for all participants to introduce them to the WI program, and study-related smartphone and smartwatch. Participants will be loaned an Android-based smartphone and smartwatch. Participants will be asked to wear the smartwatch every day for ≥12 hours. Participants are expected to wear the smartwatch for at least 6 days of the week to assist with good quality data collection for the study. They will be asked to charge the smartphone and smartwatch nightly. Participants can leave the smartphone at home. Once smartphone and smartwatch setup is complete, participants will be instructed to continue with their normal daily routine for 2 weeks during baseline data collection. With regard to the WI and WI+JITAI arms, at the end of the study, the research team will send the participants a return postal packet for them to return the study-related smartphone and smartwatch.

##### WI Program

Participants will access the 14-week WI program. Participants will receive reminders on the smartwatch to access the WI program. Furthermore, the study team will emphasize features such as badges for completing weekly modules to promote engagement with the WI program.

##### WI Arm

Participants in the WI arm will take part in the WI program mentioned above. They will also have access to the minutes of moderate-intensity PA performed over the last 7 days on their study smartphone. After the WI program is completed in week 16, the participants will transition to the PA sustainability phase (weeks 17-24), which will include participants having continued access to the WI program and PA performed over the last 7 days.

##### WI+JITAI Arm

Participants in the WI+JITAI arm will also take part in the WI program. They will have access to minutes of moderate-intensity PA performed over the last 7 days on their study smartphone, just-in-time feedback, and PA recommendations that are informed by PA guidelines for adults with SCI [43] on their smartwatch, and near–real-time minutes of PA performed over the day on their smartwatch. After the WI program is completed in week 16, the participants will transition to the PA sustainability phase (weeks 17-24), which will include participants having continued access to the WI program and feedback and recommendations on their study smartphone and smartwatch.

#### Compensation

Participants will receive gift cards for a total value of US $160 for completing the study. The participant incentives are provided upon completion of meetings and data collection. The incentives are divided into US $20 per meeting for the initial and final meetings of the study and US $20 for every 4-week duration of the study for a 24-week study.

### Statistical Analysis

#### Overview

For all aims, descriptive statistics will be obtained to assess distributional assumptions, and any transformations will be applied if needed. In addition, we will examine patterns of missingness and handle this appropriately through either multiple imputation or using models that can appropriately handle missingness (eg, mixed-effects models). We will also examine whether there are any group differences on baseline covariates (eg, pain, fatigue, health, and activity history) despite randomization, and if so, we will statistically control for these variables in our models. All analysis will be performed with an α level of .05.

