### Sample Size Determination

Sample size calculation for the primary aim (a 2-arm randomized controlled trial) indicated that 82 participants are needed per group to detect at least a standardized mean difference of 0.44 [48] (considered small to moderate) in the primary outcome, with 80% power (assuming a 2-sided test with an α level of .05). On the basis of prior research [49,50] and our pilot study [24], we anticipate a 20% dropout rate. Thus, we plan to recruit a total of 196 participants with SCI (98 participants per group). In addition, power analysis for the secondary aim (an MRT) based on 2 randomizations per day indicated that a sample size of 69 is needed to detect a difference between JITAI message and no message on the proximal PA achieved for the WI+JITAI arm [30,51]. We assumed an average proximal treatment effect for message versus no message of 0.10 (considered small) that starts with 0.12 (ie, a small effect) and decreases linearly for the 16 weeks, an α level of .05, and 80% power [30]. We will have sufficient power for the MRT given we plan to recruit 98 individuals for the WI+JITAI arm to ensure that the primary aim is powered.

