#### Primary Aim Analysis

We hypothesize that the integration of WI+JITAI will produce significantly higher PA levels over 14 weeks than the standard WI alone. Exploratory outcomes include long-term PA (measured via sensors and self-report) over 24 weeks (approximately 6 months). To test our hypothesis, we will fit a mixed-effects model in which the group indicator variable is a predictor, and the outcomes are the PA measurements at 2, 8, and 16 weeks. We will include an interaction with time in the model because we hypothesize that although PA levels may increase in both groups, they will increase more in the WI+JITAI group. We will also include a random intercept and slope for time. To evaluate long-term PA, we will include the PA levels at 24 weeks in the model.

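### Covariates enter the models only if the randomized arms happen to differ at baseline, so the primary model's covariate set is picked by chance imbalance, not prognostic value

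*Protocol article*

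**What the plan says.** The overview of the Statistical Analysis section, introduced as applying to all aims, contains this rule: "We will also examine whether there are any group differences on baseline covariates (eg, pain, fatigue, health, and activity history) despite randomization". The consequence of finding a difference is stated next: "and if so, we will statistically control for these variables in our models". It gives no definition of a difference.

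The Primary Aim Analysis specifies a mixed-effects model with a group indicator, in which "the outcomes are the PA measurements at 2, 8, and 16 weeks". It adds: "We will include an interaction with time in the model". There is also a random intercept and a random slope. No baseline covariate is named.

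Allocation and Blinding places randomization after baseline data collection and blocks it by level of injury (tetraplegia versus other). That factor is not named as a term in the primary model. Under Research Design, baseline is weeks 1 and 2, so the week-2 PA value is a pre-allocation measurement that serves as an outcome.

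The sample size statement is that "82 participants are needed per group to detect at least a standardized mean difference of 0.44". The settings given for this figure are 80% power and a two-sided α of .05.

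**The concern.** Because allocation is random, looking for baseline differences between arms looks for something already known to be chance. Adjustment helps in proportion to how well a covariate predicts the outcome, whether or not the arms differ on it. A rule keyed to imbalance leaves out strong predictors that happen to be balanced and brings in weak ones that happen not to be. The stratification factor is especially unlikely to be selected, because the blocking is there to balance it.

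At stake are precision from data already being collected, and a primary analysis whose covariates are known before the arms are compared. This is a rule the article states, not a detail left to an unseen analysis plan.

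**Working it through.** **Inputs from the article:** standardized difference 0.44, 82 per group, 80% power, two-sided α .05; visits at weeks 2, 8 and 16; group-by-time term; random intercept and slope.

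**Assumed, because the article gives no figure:** a p<.05 trigger; independent covariates; R² of 0.10 to 0.50 with the outcome level and 0 to 0.25 with change; baseline to follow-up correlation of 0.3 to 0.7.

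**1. The plan's own figure.** n = 2(1.960 + 0.842)²/0.44² = 2 × 7.849/0.1936 = 81.1, rounded up to 82 per group. This matches. It uses SD 1 and no covariates, so the stated 80% does not rely on adjustment. The rule can only forgo a gain.

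**2. How often chance selects something.** P(at least one) = 1 − 0.95^k: 5% for k = 1, 19% for k = 4, 37% for k = 9, 46% for k = 12. Positive correlation among covariates would lower these.

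**3. Single-endpoint comparison.** Simulation with 82 per arm, difference 0.44 and 6,000 trials per setting. Each cell gives one covariate / four covariates.

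| R² | Power, imbalance rule | Power, fixed adjustment | Type I error, imbalance rule |
|---|---|---|---|
| 0.10 | 79.3% / 80.4% | 82.9% / 82.6% | 4.8% / 4.4% |
| 0.25 | 80.2% / 80.3% | 89.3% / 88.9% | 4.9% / 5.0% |
| 0.50 | 82.2% / 82.7% | 97.8% / 97.7% | 3.8% / 3.4% |

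The gap is about 3, 9 and 15 points. Simulation error is about 0.5 point for power (√(0.8 × 0.2/6000)) and 0.3 point for type I error. In all six null settings the rule rejected less often than the unadjusted test on the same simulated trials. A further simulation (78 per arm, six candidates, two of them prognostic, joint R² 0.25) gave type I error 4.2% against 5.0%, and power 78% against 88%.

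**4. The group-by-time term actually planned.** Three visits, 82 per arm, complete data, 300 trials per setting. Power with no covariate, with the covariate as a main effect, and with the covariate plus its interaction with time:
- Covariate predicts level only: 80%, 80%, 80%.
- Covariate predicts level and trend: 72%, 72%, 79%.
- The same with a weaker level effect: 78%, 78%, 82%.

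Simulation error is about 2.3 points, but the mean standard errors show the same pattern. In the second setting they are 0.133, 0.133 and 0.125. A main effect absorbs between-person differences in level, which the random intercept already carries.

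**5. Change score (two-visit analogue of group-by-time), imbalance rule versus fixed adjustment.** R² with change of 0: 80% vs 80%. 0.05: 79% vs 81%. 0.10: 80% vs 83%. 0.25: 81% vs 89%.

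**6. Week-2 PA as an outcome versus as a covariate.** Power = Φ(0.44√(82/2)/σ − 1.96), with σ = √(2(1 − r)) for change and σ = √(1 − r²) for ANCOVA:
- r = 0.3: 66% vs 84%.
- r = 0.5: 80% vs 90%.
- r = 0.7: 95% vs 98%.

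**The case against.** The strongest reply is that the planned model already uses much of the baseline information. Week-2 PA is an outcome, a random intercept takes up stable differences between people, and the hypothesis concerns a larger increase over time. Covariates added as main effects then change almost nothing, as step 4 shows. This stands, and it limits what can be claimed about power.

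A reader might infer from step 3 that the trial loses about ten points of power. The documents do not support that: the figure comes from a single-endpoint comparison with an assumed R², and the Primary Aim Analysis points to the interaction.

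A reader might also infer that adjusting after seeing imbalance inflates false positives. It does not under a p<.05 trigger; the error rate is at or slightly below nominal. The simulations do not cover discretionary choice where no threshold is set.

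Nor is the whole primary model chosen by chance. Visits, group, time, interaction and random effects are fixed; only the extra covariates are open.

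Finally, a closed covariate list and a definition of a difference are ordinary analysis-plan content, so their absence from an article is no fault. What remains is the criterion itself, which the article states and which is the wrong one.

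**Conclusion.** The point holds in limited form. The plan selects covariates by observed imbalance between randomized arms, and so leaves the covariate set of the primary model undetermined until the arms are compared. The rule gives no protection that fixed adjustment for prognostic covariates would not give better.

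The cost in power cannot be fixed from the document. For the group-by-time effect it is about zero when covariates enter only as main effects. It becomes material only if covariates predict change and enter with time (about 3 points at R² 0.10 with change, 8 to 9 at 0.25), or if baseline PA is conditioned on (2 to 18 points over r = 0.7 to 0.3). These sizes rest on the assumed correlations and, for the imbalance rule, on the assumed p<.05 trigger. The stated 80% power is not undermined by this point.

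**What to change.** - Delete the imbalance-triggered rule.
- Prespecify a short covariate list for the primary model: at least level of injury, because it is the stratification factor, plus one or two variables expected to predict PA. State that each enters with its interaction with time, whatever the observed balance.
- Choose one role for week-2 PA. One option is to use it as a covariate with weeks 8 and 16 as outcomes. The tested contrast must then be a group difference at a named visit, since group-by-time would describe only the change from week 8 to week 16. With one value per visit, a random intercept, slope, their covariance and a residual variance are four parameters against three covariance elements, so the covariance structure would need simplifying. The other option keeps week 2 as an outcome and constrains baseline means to be equal across arms. Allocation after baseline justifies this, and it stays closer to the present model. Do not do both.
- Report baseline characteristics descriptively, and keep adjustment for any visibly imbalanced variable as a sensitivity analysis.

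The cost is a small respecification of the primary model and a few degrees of freedom. No extra participants or data are needed. The team gives up adding an imbalanced variable to the primary model after the fact.

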#### Primary Aim Analysis

We hypothesize that the integration of WI+JITAI will produce significantly higher PA levels over 14 weeks than the standard WI alone. Exploratory outcomes include long-term PA (measured via sensors and self-report) over 24 weeks (approximately 6 months). To test our hypothesis, we will fit a mixed-effects model in which the group indicator variable is a predictor, and the outcomes are the PA measurements at 2, 8, and 16 weeks. We will include an interaction with time in the model because we hypothesize that although PA levels may increase in both groups, they will increase more in the WI+JITAI group. We will also include a random intercept and slope for time. To evaluate long-term PA, we will include the PA levels at 24 weeks in the model.

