### Research Design

#### Overview

Participants will take part in the study from their home environment in the community. The study has three phases: (1) baseline (weeks 1 and 2); (2) WI program with or without JITAI (weeks 3-16); and (3) PA sustainability (weeks 17-24). Participants will provide survey-based information at various time points during the 24-week study. Participants will be asked to wear a smartwatch every day for ≥12 hours for the duration of the study. The PA intervention for this study is informed by the capability, opportunity, and motivation (COM-B) model, which highlights that these 3 constructs should be considered when developing a behavioral intervention [31]. To our knowledge, this is the first study to optimize a JITAI that has the potential to boost PA levels using real-time feedback for individuals with SCI.

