#### Allocation and Blinding

After the baseline data collection, participants will be randomly allocated to one of 2 study arms (WI arm or WI+JITAI arm) based on the randomization schedule established by the project biostatistician. Participants will be block randomized on the basis of their level of injury: tetraplegia (higher-level injury) versus other (lower-level injury).

Participants will be masked (single blinding) to the study arm. All participants will receive the same WI program and commercial off-the-shelf technology. Participants in both arms will have access to minutes of moderate-intensity PA performed over the last 7 days, which is designed to motivate them to use the smartwatch in the community. In addition, the participants in the WI+JITAI arm will receive randomized prompts of various types of tailored feedback and PA recommendations over the course of the study.

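### Week 2 is measured before randomization but modelled as an outcome with a free group difference, so the likely primary test makes inefficient use of the baseline

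*Protocol article*

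**What the plan says.** All references are to the Protocol article.

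- **Timing.** Research Design, Overview, lists the first phase as "1) baseline (weeks 1 and 2". Allocation and Blinding adds: "After the baseline data collection, participants will be randomly allocated to one of 2 study arms". The week-2 measurement therefore precedes randomization.
- **Model.** In Primary Aim Analysis, "the group indicator variable is a predictor, and the outcomes are the PA measurements at 2, 8, and 16 weeks". The section adds an interaction with time, on the ground that PA should rise more with the JITAI, and a random intercept and slope for time. It states no equality of arms at week 2 and does not name the coefficient that decides the hypothesis.
- **Baseline adjustment.** Statistical Analysis, Overview, provides for adjustment only when a group difference on a baseline covariate is found. Week-2 PA is not a planned covariate.
- **Sizing.** Sample Size Determination states that "82 participants are needed per group to detect at least a standardized mean difference of 0.44", "with 80% power (assuming a 2-sided test with an α level of .05". It gives no time point, no correlation and no number of repeated measures, and does not say whether 0.44 is a difference in level or in change.

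**The concern.** Randomization makes the expected group difference at week 2 zero. A model with a free group term ignores this: it estimates the chance difference and in effect subtracts it in full from the later difference. The noise of the baseline measurement then enters the treatment comparison. Setting the week-2 difference to zero, or adjusting for week-2 PA, removes only the part of the baseline that predicts follow-up, and so gives a smaller standard error from the same data.

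The article's reason for the interaction, a larger increase in one arm, points to that term as the primary test. The other candidate, the group main effect, would be worse. With time counted from week 2, it estimates the pre-randomization difference itself. What is at stake is precision, and clarity about which coefficient decides the trial.

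**Working it through.** **Inputs.** From the article: 82 analysed per arm, effect 0.44 SD, two-sided alpha 0.05, measurements at weeks 2, 8 and 16. Assumed, because the article gives nothing: correlation rho equal between all pairs of weeks (compound symmetry), SD 1 at each week, and a group difference that is zero at week 2 and grows linearly to 0.44 at week 16. Whether 98 recruited per arm leave 82 after dropout is a separate matter and is not used here.

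**1. The plan's own figure.** Two independent means at one time point:

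n = 2(1.960 + 0.842)² / 0.44² = 81.08, rounded up to 82 per arm.

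The stated figure reproduces. Power at 82 is 80.4% and does not depend on rho.

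**2. Free-baseline slope.** Scale time as t = (week − 2)/14, giving 0, 0.4286 and 1. The sum of squared deviations from the mean is 0.5034. With free group and interaction terms,

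Var(free) = 2(1 − rho) / (0.5034 n) = 3.973(1 − rho)/n.

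The week-16-minus-week-2 change score has variance 4(1 − rho)/n, so the two are almost the same test.

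**3. Baseline-constrained slope.** With the group difference fixed at zero at week 2,

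Var(constrained) = 2/(n A), where A = [Σt² − rho(Σt)²/(1 + 2 rho)]/(1 − rho), Σt² = 1.1837 and (Σt)² = 2.0408.

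At rho 0.5, A = (1.1837 − 0.5102)/0.5 = 1.347.

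**4. Worked case, rho 0.5, n = 82.** Free: SE = √(3.973 × 0.5/82) = 0.1557, 0.44/0.1557 = 2.83, power 80.7%. Constrained: SE = √(2/(82 × 1.347)) = 0.1346, 0.44/0.1346 = 3.27, power 90.5%.

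**5. Across rho.**

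| rho | Power, free slope | Power, constrained slope | n per arm for 80%: free / constrained |
|---|---|---|---|
| 0.3 | 66.6% | 85.4% | 113 / 71 |
| 0.4 | 73.3% | 87.5% | 97 / 67 |
| 0.5 | 80.7% | 90.5% | 81 / 61 |
| 0.6 | 88.5% | 94.2% | 65 / 52 |
| 0.7 | 95.4% | 97.6% | 49 / 42 |
| 0.8 | 99.4% | 99.7% | 33 / 30 |

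**6. Where the planned test crosses 80%.** The free slope needs 81.08 × (3.973/2)(1 − rho) per arm. Setting this equal to 82 gives rho = 0.49.

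**7. Other covariance structures.** Correlation that decays with time gives the same pattern (rho 0.5 between weeks 2 and 16: 80.4% versus 90.2%). In six random intercept-and-slope settings, closer to the stated model, the week-2 to week-16 correlation ran from 0.42 to 0.74. The free slope's variance was 1.09 to 1.35 times the constrained one, with power 76.9% to 97.9% free and 87.9% to 98.7% constrained.

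**8. A different trajectory.** If the full 0.44 SD is reached by week 8 and then holds, at rho 0.5 under compound symmetry the free slope estimates 0.416 (power 76.2%) and the constrained slope 0.467 (93.4%).

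**The case against.** The strongest reply has four parts.

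- **A free-baseline mixed model is valid.** This stands. Under randomization the estimate is unbiased, and the loss is one of efficiency only.
- **The loss may be small.** This also stands. No rho is given. At 0.7 the gap is about two points, and above about 0.5 the planned test has more power than the 80.4% of the comparison in step 1. A reader might infer that the trial is underpowered; the article does not support that.
- **A mismatch with the sizing is not shown.** A reader might infer that the primary test is not the contrast that was sized, because 82 reproduces from a simple two-sample formula. But the article says only "to detect at least a standardized mean difference of 0.44", and the same formula gives 82 whether 0.44 is a level or a change. If it is a change, the planned test broadly matches. A mismatch is possible, no more.
- **The deciding coefficient and the coding of time are details for an analysis plan.** This stands in part. That the interaction is primary, with time linear, is a strong inference and not a statement. Categorical time is optional. But the article does more than leave the baseline open: it places week 2 among the outcomes, adds a group term, and makes covariate adjustment depend on observed imbalance.

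**Conclusion.** The point holds as one of efficiency. The article affirmatively models a pre-randomization measurement as an outcome with a free group difference. If the interaction is the primary test, it has less power than a baseline-constrained analysis of the same data at every correlation examined: about 19 points less at rho 0.3, 10 at 0.5 and 2 at 0.7, with 82 per arm. These sizes rest on compound symmetry and on a difference growing linearly to 0.44 SD. Serial decay and random-slope structures keep the direction. Power falls below the stated 80% only if rho is under about 0.5. Neither bias, nor inadequate power, nor a definite conflict with the sample size calculation is established. The change is worth making because it uses measurements already planned and randomization justifies it.

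**What to change.** Reword Primary Aim Analysis in two respects.

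1. **Use the baseline properly, whatever imbalance is observed.** Either keep week 2 in the outcome vector with equal means across arms (no group main effect, time coded zero at week 2), or make week-2 PA a prespecified covariate with weeks 8 and 16 as outcomes.
2. **Name the deciding coefficient.** It could be the constrained group-by-time term or the week-16 group difference. Under linear growth they perform alike (85.4% versus 84.0% at rho 0.3, the latter from a baseline-adjusted week-16 comparison). With week as categories, the week-16 difference does not depend on a linear trajectory, but it narrows the question to one time point.

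Stating whether 0.44 is a level or a change would settle the open question about the sizing.

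The cost is analysis wording only, with no new data or visits. The article reports that enrollment is ongoing and that no interim analysis is planned, so the change can be made before analysis.

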### Objectives

The overarching goal of this study is to investigate the benefits of combining an mHealth-based JITAI with the NCHPAD’s 14-week web-based PA intervention (WI) program for increasing and sustaining moderate-intensity or higher PA levels among individuals with SCI. This protocol outlines the study design for investigating the impact of integrating a JITAI with the WI program via a randomized controlled trial that integrates a 2-arm trial and a microrandomized trial (MRT). Specifically, individuals with SCI (N=196) will be randomized to either a WI program or a WI program combined with the JITAI (WI+JITAI). Within the WI+JITAI arm, an MRT [27,29,30] will be used to microrandomize participants several times a day to various types of feedback and PA recommendations. The primary aim is to investigate the long-term benefits of adding a JITAI to WI. We hypothesize that the integration of a JITAI into WI will produce significantly higher PA levels than those with WI alone. The secondary aim is to investigate the benefit of just-in-time PA feedback on proximal PA. Proximal PA is defined as moderate-intensity PA within 120 minutes of a PA feedback prompt. The exploratory aim will investigate time-invariant moderators such as biological sex and level of injury and time-varying moderators such as prior PA and engagement with the JITAI to help identify subgroups of individuals with SCI who are likely to benefit the most from the integration of a JITAI with WI.

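### Adding week 24 to a single-slope model cannot show whether the gain is sustained after week 16, and the Objectives should be aligned with the exploratory status of 24-week physical activity

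*Protocol article*

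**What the plan says.** Primary Aim Analysis tests the main hypothesis with a mixed-effects model on physical activity (PA) at weeks 2, 8 and 16, with a group indicator and an interaction with time. On the form of time it adds: "We will also include a random intercept and slope for time". The only long-term analysis described is the same model with one more time point: "To evaluate long-term PA, we will include the PA levels at 24 weeks in the model". It mentions no phase term, knot, categorical visit or comparison of week 24 with week 16.

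The design itself changes phase at week 16. The WI+JITAI Arm section says: "After the WI program is completed in week 16, the participants will transition to the PA sustainability phase". The Research Design overview and the WI Arm section give the same phase, weeks 17-24. Both arms keep access to the web programme in that phase, and the WI+JITAI arm keeps its feedback and recommendations.

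On status, the Objectives say "The primary aim is to investigate the long-term benefits of adding a JITAI to WI". Primary Aim Analysis instead states a 14-week hypothesis and says "Exploratory outcomes include long-term PA (measured via sensors and self-report) over 24 weeks".

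**The concern.** The overarching goal in the Objectives is both to raise PA and to sustain it. Sustaining is a question about weeks 17-24: does the between-arm difference reached by week 16 hold, shrink or disappear by week 24? A single group-by-time slope has one number for the whole period from week 2 to week 24. If the difference grows to week 16 and then flattens or falls, the line averages the two phases. Any positive slope then implies a difference that is still widening at week 24, whatever happened after week 16. A partial loss could be reported as continuing growth.

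The wording conflict is a separate and smaller matter. The Objectives call long-term benefit the primary aim, while the analysis section uses the same term for an exploratory outcome.

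**Working it through.** **1. The plan's own figure.** Sample Size Determination says "82 participants are needed per group to detect at least a standardized mean difference of 0.44", with 80% power and two-sided α = .05. Check: n = 2(1.960 + 0.842)² / 0.44² = 15.70 / 0.1936 = 81.1, so 82 per arm. The t-based value is 82.05, and power at 82 is 0.804 (normal) or 0.800 (t). The figure reproduces, so 0.44 SD is used below as the week-16 difference. Of the 98 recruited per arm, 98 × 0.80 = 78.4, so 78 remain after the stated dropout ("we anticipate a 20% dropout rate").

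**2. Assumed truth.** The week-2 difference is 0, because Allocation and Blinding places randomization after baseline data collection. The difference then rises linearly to 0.44 SD at week 16, which gives 0.44 × 6/14 = 0.19 at week 8. Week 24 is varied: 0.44 (kept), 0.22 (half lost), 0 (all lost). The documents give none of these later values; they are scenarios.

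**3. Fitted line.** With weeks 2, 8, 16 and 24, the mean is 12.5 and Sxx = 110.25 + 20.25 + 12.25 + 132.25 = 275. The slope is Σ(t − 12.5)d / 275, with weights −0.0382, −0.0164, +0.0127 and +0.0418 on the four differences. Ordinary least squares and GLS with a random intercept and slope give the same line, so these fitted values do not depend on the variance assumptions.

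| True week 24 | Slope per week | Fitted week 16 | Fitted week 24 | Fitted change, 16 to 24 | True change |
|---|---|---|---|---|---|
| 0.44 (kept) | 0.0209 | 0.34 | 0.51 | +0.17 | 0 |
| 0.22 (half lost) | 0.0117 | 0.25 | 0.35 | +0.09 | −0.22 |
| 0 (all lost) | 0.0025 | 0.17 | 0.19 | +0.02 | −0.44 |

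In both loss scenarios the fitted change has the wrong sign.

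**4. How often the slope would be significant.** Assume unit variance and equal correlation 0.5, with 78 per arm. The SE of the slope difference is √(2 × 0.5 / (78 × 275)) = 0.00683.
- Half lost: z = 0.0117 / 0.00683 = 1.72, and Φ(1.72 − 1.96) is about 0.40.
- All lost: z = 0.37, and the two-sided rejection rate is about 0.065.
- Kept: z = 3.06, and power is about 0.86.

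With 82 per arm and two assumed sets of random-slope variances, the chance of a significant positive slope is 0.33-0.39 (half lost), about 0.05 (all lost) and 0.77-0.85 (kept).

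**5. After the change.** A categorical visit, or a knot at week 16, returns the true week-16-to-24 changes in these three scenarios: 0, −0.22 and −0.44 SD.

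**The case against.** **Linearity is inferred.** The article never uses the word linear, and a categorical fixed time effect with a random slope is a standard model. A fuller analysis plan could specify that. This stands as a caveat. Still, a single interaction with time together with a slope for time most plainly means linear time, and the article offers no other long-term analysis.

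**Week 16 does not end the randomized contrast.** JITAI feedback continues through week 24, the JITAI Components section gives a 22-week intervention period, and both arms keep web-programme access. This stands too. The question is maintenance under continued JITAI, not after withdrawal, and a break in the between-arm difference at week 16 is possible rather than certain. The phase boundary is nevertheless the protocol's own, and the model should be able to show a change there.

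**Complete loss would probably not be declared a benefit.** Correct: the slope test then rejects only about 5-7% of the time. The half-lost case is the more troublesome one.

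**Power.** A reader might infer that the single slope also wastes power. The material does not support that as a general claim, since the answer depends on the profile and on how baseline is handled. For the gradual rise that is then kept, the slope has about 86% power, against about 78% for the unconstrained categorical change from week 2 to week 24 (0.44 / √(4 × 0.5 / 78) = 2.75).

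**The deciding test.** A reader might infer from the conflicting labels that it is open which analysis decides the trial. It is not: Primary Aim Analysis ties the hypothesis test to weeks 2, 8 and 16 and calls 24-week PA exploratory.

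**Conclusion.** The point holds for the exploratory 24-week analysis. As plainly read, the model cannot separate growth to week 16 from maintenance or decline in weeks 17-24. Under the assumed profile it overstates the week-16-to-24 change in the group difference by 0.17 SD (gain kept), 0.31 SD (half lost: 0.09 + 0.22) and 0.46 SD (all lost: 0.02 + 0.44). If all the gain is lost, the fitted week-24 difference is still +0.19 SD. If half is lost, the 24-week slope is significant about 40% of the time at 78 per arm and correlation 0.5, or 33-39% under the other variance assumptions tried at 82 per arm.

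These sizes rest on linear time and on the assumed rise to 0.44 SD. The fault is lack of fit; week 24 is observed and enters the model, so the line does not reach beyond the data. The primary test on weeks 2, 8 and 16 is not affected. The conflict between the Objectives and Primary Aim Analysis is real but is a matter of wording.

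**What to change.** For the exploratory 24-week analysis, fit week as a category (2, 8, 16, 24) or as piecewise linear with a knot at week 16, each interacting with group. Report two quantities with confidence intervals: the week-24 group difference, and its change from week 16. State that both describe maintenance under continued JITAI. The categorical form is safer if gains come early, because the knot still assumes a straight rise to week 16.

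In the Objectives, reword the primary aim so that the 14-week effect (weeks 2 to 16) is the primary test and 24-week PA is exploratory, as Primary Aim Analysis already has it.

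Cost: the single-slope model has 4 fixed effects. The knot makes 6 (2 more) and the categorical form 8 (4 more, or 3 with a common baseline mean). For some profiles power is somewhat lower than for the slope. The change from week 16 to week 24 will also be imprecise: at 82 per arm, power to detect loss of half the gain is about 0.29 if the week 16-24 correlation is 0.5 and about 0.61 if it is 0.8, a correlation the article does not give. So the estimate and interval should carry the message. No new data are needed, and with no interim analysis planned the change can be made before any outcome comparison.
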